#### CSF

The following CSF variables will be analyzed according to previously described methods [15, 31–33]: Aβ40, Aβ42, t-tau, p-tau (phosphorylated at Thr181), α-syn, NFL, 3-methoxy-4-hydroxyphenylethyleneglycol (MHPG), 5-hydroxyindolacetic acid (5-HIAA), homovanillic acid (HVA), blood pigments and the total cell count. The cell count and blood pigments will be analyzed within 2 h after CSF collection; α-syn will be analyzed according to previously described methods [32]; all other parameters will be analyzed within 4 weeks after CSF collection. CSF samples are collected in polypropylene tubes, centrifuged, aliquoted, and stored at − 80 °C until analysis. Because the concentrations of HVA and 5-HIAA vary in the different fractions of CSF, we aim for separate collection of the 9th–11th ml fraction for analysis of neurotransmitter metabolites, according to previously described methods [34]. Laboratory technicians blinded for clinical symptoms and outcome will perform all CSF analyses. When patients are taking dopaminergic medication at the time of lumbar puncture, the results of neurotransmitter metabolites will be excluded from the measurements.

### Assessment of diagnoses

Before inclusion, the referring neurologist will be asked to establish the probable diagnosis based on routine clinical examination. Specifically, a level of diagnostic (un) certainty will be indicated on a scale of 0–100. After inclusion, a movement disorder expert will also be asked for the diagnosis and level of certainty based on the clinical evaluation; a neuroradiologist makes the diagnosis based on imaging findings and a neurochemist based on CSF analysis.

The final clinical diagnosis will be established after three years of follow-up in consensus by two independent neurologists specialized in movement disorders, and this will serve as the “silver standard” reference diagnosis. This reference diagnosis will be based on the clinical data at baseline, the disease course after 3 years follow-up and with adherence to the following international clinical criteria: Movement Disorder Society clinical diagnostic criteria for PD [35], Gilman criteria for MSA [36], the movement disorder society criteria for PSP [37]**,** Armstrong criteria for CBS [38] and Zijlmans criteria for vascular parkinsonism [39]**.** These neurologists will be blinded for the results of the ancillary investigations, except for the conventional MRI because this is part of routine procedures in clinical practice. See Fig. 1 for a flowchart of the study design.

**Fig. 1 Fig1:**
[figure not shown]
flowchart of the study design. *A translated version of the structured questionnaires are provided as Additional file 1 with this article

### Outcome measures

Our primary outcome measure of interest will be the diagnosis (e.g. PD or AP) after three years of follow-up. The secondary outcome measure is the specific diagnosis (PD, MSA, PSP, etc.) after three years of follow-up.

### Statistical analysis

For our first objective, the estimated initial diagnosis by the movement disorder specialist, neuroradiologist and neurochemist respectively will be compared to the reference diagnosis (after three years follow-up). Sensitivity, specificity and Kappa (k) are calculated. Next, the Net Reclassification Index (NRI) is calculated, which gives the proportion of participants correctly (re-)classified as having PD or AP. NRI values will be calculated for MRI and CSF *following* the classification by a movement disorder specialist [40].

For our second objective, descriptive data will be generated for all variables. Continuous variables will be presented as means ± standard deviations or medians. PD patients will be compared with AP patients using a Student’s t or Mann-Whitney U test, whichever appropriate.

Dichotomous variables will be compared using Chi-square test or Fisher exact test, whichever appropriate. A *p*-value of < 0.05 will be considered significant (two-sided).

For each diagnostic strategy (e.g. clinical evaluation, MRI and CSF respectively) blockwise logistic regression with stepwise forward model selection will be used to identify parameters with optimal diagnostic power. For each model ROC-curves and C-statistics are calculated.

Data management and analysis will be performed using IBM SPSS Statistics 22 (IBM Corp, Armonk, NY, USA).

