**Methods/design:**

Patients with parkinsonism with an uncertain clinical diagnosis and a disease course less than three years will be recruited. Patients will undergo extensive neurological examination, brain MRI including conventional and advanced sequences, and a lumbar puncture. The diagnosis (including level of certainty) will be defined by a movement disorders expert, neuroradiologist and neurochemist based on clinical data, MRI results and CSF results, respectively. The clinical diagnosis after three years’ follow-up will serve as the “gold standard” reference diagnosis, based on consensus criteria and as established by two movement disorder specialists (blinded to the test results). Diagnostic accuracy of individual instruments and added value of brain MRI and CSF analysis *after* evaluation by a movement disorder expert will be calculated, expressed as the change in percentage of individuals that are correctly diagnosed with PD or AP.

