### Sample size calculation

This study is exploratory in nature. We estimate that a minimum of 30 AP and 30 PD patients will be needed to evaluate the diagnostic value of the three diagnostic strategies (clinical evaluation by a movement disorder specialist, MRI and CSF biomarkers). In our previous cohort study of patients with parkinsonism 60% of patients had a diagnosis of AP [34]. 30% of patients did not complete the follow-up period of 3 years, mainly because the participant had deceased or was too severely affected, the majority of which was diagnosed with AP (33 out of 46 drop-outs). Therefore, we estimate that approximately 100 participants will be needed to assess the diagnostic accuracy of the different diagnostic tests.

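### The NRI is described as a proportion of participants; the standard NRI is a sum of two group-specific proportions and would run at about twice the change in percentage correct that the abstract promises

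*Protocol article*

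**What the plan says.** In the Statistical analysis section, the diagnoses of the movement disorder specialist, the neuroradiologist and the neurochemist are each compared with the reference diagnosis by sensitivity, specificity and kappa. The NRI comes next, described as the statistic "which gives the proportion of participants correctly (re-)classified as having PD or AP". The section continues that "NRI values will be calculated for MRI and CSF" following the specialist's classification. It gives no formula, no weighting by group size and no separate AP and PD components.

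The abstract (Methods/design) says that the added value of MRI and CSF after the expert's evaluation will be "expressed as the change in percentage of individuals that are correctly diagnosed with PD or AP".

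The case mix comes from the Sample size calculation: "a minimum of 30 AP and 30 PD patients will be needed"; in the previous cohort "60% of patients had a diagnosis of AP" and "30% of patients did not complete the follow-up period of 3 years", most of the losses being AP ("33 out of 46 drop-outs"); hence "we estimate that approximately 100 participants will be needed".

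**The concern.** The two-category NRI adds two proportions that have different denominators: AP patients in one, PD patients in the other. The sum is not a proportion of participants. Nor is it the change in percentage correctly diagnosed, which weights each group by its size. The article therefore names one statistic, describes it as another, and promises the second in the abstract. This is a wrong statement about a named statistic, not a detail left to a fuller document.

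It matters because the NRI is the only statistic the section applies to MRI and CSF on top of the specialist's judgement. The article wants its results to help neurologists choose a diagnostic strategy, and it notes that MRI is expensive and that CSF needs a lumbar puncture. An NRI of 0.20 reported under the article's description would be read as 20% of patients, when about 10% more were correctly diagnosed.

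**Working it through.** **Case mix at analysis.** The article gives no numeric NRI or accuracy target. The only figure to reproduce is the sample size, used here to obtain the AP:PD mix.

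- Inputs (Sample size calculation): 60% AP at entry, 30% drop-out, 33 of 46 drop-outs AP, about 100 entered.
- Entrants needed for 30 PD completers: 30 / (0.40 - 0.30 × 13/46) = 95.2.
- Entrants needed for 30 AP completers: 30 / (0.60 - 0.30 × 33/46) = 78.0.
- With drop-out the same in both groups, 30 PD would need 30 / 0.40 / 0.70 = 107.1, so 108.
- The stated figure of about 100 is not reproduced exactly. It lies between 96 and 108, is plainly rounded, and is not at issue here.
- Completers from 100 entrants: AP 60 - 30 × 33/46 = 38.5; PD 40 - 30 × 13/46 = 31.5. The AP share is 38.5/70 = 0.55.

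**Formulas.** Let π be the AP share among those analysed, ΔSe the net number of AP patients corrected divided by all AP, and ΔSp the same for PD.

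- NRI = ΔSe + ΔSp, range -2 to +2.
- Change in proportion correct = π·ΔSe + (1 - π)·ΔSp.
- If only AP patients move, the ratio of the two is 1/π. If only PD patients move, it is 1/(1 - π). If ΔSe = ΔSp, it is 2. When ΔSe and ΔSp do not have opposite signs, the ratio lies between 1/π and 1/(1 - π).

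**Size of the ratio.**

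- π = 0.50 (30:30): exactly 2.00, whatever the pattern of movement.
- π = 0.55 (expected completers): 1/0.55 = 1.82 to 1/0.45 = 2.22.
- π = 0.60 (entry mix kept to the end): 1/0.60 = 1.67 to 1/0.40 = 2.50.

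**Worked counts.** The documents give no reclassification counts, so these are illustrative.

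| AP:PD | Net corrected AP, PD | NRI | Change in proportion correct |
|---|---|---|---|
| 30:30 | +4, +3 | 4/30 + 3/30 = 0.233 | 7/60 = 0.117 |
| 38:32 | +4, +3 | 4/38 + 3/32 = 0.199 | 7/70 = 0.100 |
| 38:32 | +6, 0 | 6/38 = 0.158 | 6/70 = 0.086 |
| 38:32 | 0, +6 | 6/32 = 0.188 | 6/70 = 0.086 |
| 38:32 | +12, -11 | 12/38 - 11/32 = -0.028 | 1/70 = +0.014 |
| 42:28 | +6, -4 | 6/42 - 4/28 = 0 | 2/70 = +0.029 |
| 42:28 | +6, -5 | 6/42 - 5/28 = -0.036 | 1/70 = +0.014 |

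The article's description, taken literally, also allows a gross count. If the first row arose from 6 AP corrected and 2 made wrong, and 5 PD corrected and 2 made wrong, the proportion corrected is 11/60 = 0.183. One data set then gives 0.233, 0.117 or 0.183 depending on the reading.

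**Opposite signs.** The NRI and the change in proportion correct differ in sign only if ΔSe and ΔSp move in opposite directions and the proportional change in the smaller group exceeds that in the larger by a factor between 1 and π/(1 - π). That factor is at most 1.22 at π = 0.55 and 1.50 at π = 0.60. At 30:30 reversal is impossible. In simulations with assumed per-patient rates of 10-20% corrected and 5-10% made wrong, equal in AP and PD, reversal occurred in 0% at 30:30, at most 0.02% at 38:32, and 0.05% to 1.1% at 42:28. A test that systematically pulls patients towards one diagnosis would make opposite movement more common than these equal rates imply.

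**The case against.** The strongest reply is that the article may mean what it describes. Both of its descriptions point to a participant-level quantity. If that is what is computed, nothing is inflated and only the name is wrong. The article gives no formula, and the source it cites for the NRI is not at hand. This stands, and it makes the two-fold inflation conditional. It does not rescue the sentence, because either the description or the name must change.

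A reader might infer that the added-value result will be doubled or will carry the wrong sign. The documents do not support that. Doubling needs the standard NRI to be computed and then read as a share of patients. Reversal cannot happen at 30:30, the only group sizes the article states, and needs a narrow pattern at the expected mix. In the 38:32 example a test would have to gain 12 of 38 AP while losing 11 of 32 PD, and both measures are then close to zero.

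A reader might also infer that the NRI hides trade-offs that percentage correct would show. It does not work that way: with 6 AP gained and 6 PD lost, percentage correct shows exactly no change. Both are single summaries, and only the separate components show the trade-off. The sensitivities and specificities planned for each assessor give some view of this asymmetry, but they describe each assessor alone and not MRI or CSF added to the specialist's classification.

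Finally, the study calls itself exploratory, and no test, threshold or sample size depends on the NRI. That limits how serious the point is.

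**Conclusion.** The point holds as a misdescription, and that part is certain: the standard two-category NRI is not a proportion of participants and is not the measure promised in the abstract. The numerical consequence is conditional on the standard NRI being computed and read as the Statistical analysis section describes it. It would then be about twice the change in percentage correct at the planned mix. The 1.82 to 2.22 range at the expected mix assumes that drop-out follows the previous cohort and that sensitivity and specificity do not move in opposite directions. If they do, the two measures can diverge further, and a difference in sign is a rare case confined to unequal groups. The data collection, the reference diagnosis and the main accuracy analysis are untouched. It should be fixed before analysis, but it does not threaten the study.

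**What to change.** State in the Statistical analysis section which quantity is meant, and give its formula. Report the added value of MRI and of CSF after the specialist's classification as the paired change in percentage correctly classified, with a 95% CI, which is what the abstract promises. Beside it, report the paired change in sensitivity and the paired change in specificity separately, since either single summary can hide a gain in one group bought by a loss in the other. If the NRI is kept, show its AP and PD components, label it as their sum with range -2 to +2, and do not express it as a proportion or percentage of participants.

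The cost is a change of wording and a few paired 2x2 tables from data already planned. The stated added value may look smaller than an NRI would.

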#### Structured interview

Standardized questionnaires on demographics, medical history, cardiovascular risk factors, activities in daily living, medication use, disease onset, clinical signs, most affected body site, balance and fear of falling will be administered at baseline and every year during follow-up for 3 years. In addition, the Non-Motor Symptom Scale (NMSS) [22], Hospital Anxiety and Depression Scale (HADS), Questionnaire for Impulsive-Compulsive Disorders in Parkinson’s Disease (QUIP) and Epworth Sleepiness Scale (ESS) will be scored [23–25]. A translated version of the structured questionnaires are provided as Additional file 1 with this article.

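### The search for markers that separate PD from AP states no age term, so an age gap between the groups could create or hide a marker; age-adjusted results should stand beside the crude ones

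*Protocol article*

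**What the plan says.** The Objectives section makes the identification of variables that differentiate PD from AP the secondary objective, and variables that differ among the AP syndromes the third. For the second objective, the Statistical analysis section sets out these steps:

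- Continuous variables: "PD patients will be compared with AP patients using a Student" t test, with the Mann-Whitney U test as the alternative.
- Binary variables: "Dichotomous variables will be compared using Chi-square test or Fisher exact test, whichever appropriate".
- Threshold: a p-"value of < 0.05 will be considered significant (two-sided").
- Modelling, done separately for the clinical, MRI and CSF strategies: "blockwise logistic regression with stepwise forward model selection will be used to identify parameters with optimal diagnostic power". ROC curves and C-statistics follow for each model.

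The article does not list the contents of the blocks. Age appears as an entry limit (adults, with no upper bound, Table 1). It would also be on record through the interview: "Standardized questionnaires on demographics, medical history, cardiovascular risk factors" and further items are collected at baseline. No use of age in the marker analyses is stated.

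The candidate markers are numerous. The CSF section opens its list with "The following CSF variables will be analyzed according to previously described methods" and includes NFL, total and phosphorylated tau, and amyloid measures. The MRI section scores ventricular size, lobar and brainstem atrophy, perivascular spaces and white matter change, among others.

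**The concern.** A t, Mann-Whitney, chi-square or Fisher test takes no covariate. The difference it tests is the disease effect plus the age gap between the groups multiplied by the marker's slope on age. Forward selection within a strategy inherits the same mixture unless age is in the model.

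AP here pools MSA, PSP, DLB, CBS and vascular parkinsonism, and there is no matching, stratification or use of age-specific reference values that would align its age with that of PD. If AP is older, a marker that rises with age can look discriminative when it is not. If AP is younger, a real rise can be cancelled.

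At stake is which markers the study puts forward, and how the MRI and CSF C-statistics are read. Age is known without a scan or a lumbar puncture. A C-statistic that partly reflects age therefore does not show what the test contributes beyond age. The article's Discussion says the results should help neurologists choose among a specialist, MRI and CSF, so that distinction is useful.

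**Working it through.** **Group size.** The article states no figure for an age effect, so there is none to reproduce. The input it does give is the minimum of 30 AP and 30 PD. That minimum fits the stated target of about 100:

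- The earlier cohort had 156 patients, 60% with AP: 93.6 AP and 62.4 PD. Of 46 drop-outs, 33 were AP, so drop-out was 33/93.6 = 35% in AP and 13/62.4 = 21% in PD.
- For 30 PD completers at 40% PD, N = 30/(0.40 × 0.792) = 95. With a common 30% drop-out, N = 30/(0.40 × 0.70) = 107.
- About 100 lies between the two, so 30 per group is a fair size for the checks below.

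**Check 1: a CSF marker on the log scale, no disease effect.** Assumptions not in the documents: the marker rises 0.02 to 0.03 log units (about 2 to 3%) per year of age, with SD 0.4 to 0.5 on the log scale. The formulas are:

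- spurious shift d = age gap × slope / SD
- AUC = Φ(d/√2)
- chance of p < 0.05 from the noncentral t with 58 df and noncentrality d√15

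| Age gap | d, low end | d, high end | AUC | Chance of p < 0.05 |
|---|---|---|---|---|
| 0 years | 0 | 0 | 0.50 | 5% |
| 3 years | 3 × 0.02/0.5 = 0.12 | 3 × 0.03/0.4 = 0.225 | 0.53–0.56 | 7–14% |
| 5 years | 5 × 0.02/0.5 = 0.20 | 5 × 0.03/0.4 = 0.375 | 0.56–0.60 | 12–30% |
| 8 years | 8 × 0.02/0.5 = 0.32 | 8 × 0.03/0.4 = 0.60 | 0.59–0.66 | 23–63% |

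**Check 2: any continuous marker, scale-free, by simulation.** Assumptions: within-group correlation ρ between marker and age of 0.3 to 0.7, and an age gap g of 0.25 to 0.75 SD of age. The shift is then gρ marker SDs. The planned t test was compared with a linear model that adds age.

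*No true difference (4,000 runs per setting):*

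| Gap (SD) | Unadjusted p < 0.05 | Age-adjusted p < 0.05 | AUC from age alone |
|---|---|---|---|
| 0 | about 5% | about 5% | 0.50 |
| 0.25 | 6–11% | about 5% | 0.52–0.55 |
| 0.5 | 9–26% | about 5% | 0.54–0.60 |
| 0.75 | 14–53% | about 5% | 0.56–0.65 |

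Central case: g = 0.5 and ρ = 0.5 give d = 0.25 and AUC = Φ(0.25/1.414) = 0.57. The simulated rejection rate is 14.7%; the noncentral t gives 15.9%.

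*True difference of 0.8 SD, age gap in the opposite direction (3,000 runs per setting):*

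| Gap (SD) | Unadjusted power | Age-adjusted power |
|---|---|---|
| 0 | 86–87% | 88.5–98.8% |
| 0.25 | 66–78% | 87–99% |
| 0.5 | 40–70% | 87–98% |
| 0.75 | 19–60% | 84–98% |

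Central case: the visible difference is 0.8 − 0.25 = 0.55 SD, and power falls from 86% to 57%, against 92% with age in the model.

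In the first row of the last table there is no age gap, and the linear adjustment loses no power. That row concerns the linear model for marker differences; it does not carry over to the logistic models.

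**The case against.** The case for leaving the plan as it is has several parts.

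- **Block contents are not listed.** A reader might infer that the MRI and CSF models exclude age. The article does not say so, and a demographic first block would fit its wording. What can be said is that no age term is stated for the models, whereas the named two-group tests cannot hold one. Age might also be a candidate in the clinical block, but forward selection would not guarantee its entry, and it would not adjust the separate MRI and CSF models.
- **An age gap would be visible.** Descriptive data are planned for all variables, and demographics are collected. This stands, but seeing a gap does not remove its effect on the marker results.
- **The mechanism is not in the documents.** They give no group ages, no marker slopes on age and no ages at onset. That these markers vary with age is general subject knowledge used here as an assumption. Direction and size are unknown, and the 63% needs the largest gap, the steepest slope and the smallest SD together. This stands in full.
- **Crude discrimination is a proper target in a diagnostic study.** This also stands. How well a marker separates PD from AP in the intended patients is a legitimate result. Adjustment answers a second question: whether the marker adds to age.
- **The main objective is not touched.** A reader might infer that the study's diagnostic accuracy is misstated. It is not. Sensitivity, specificity and kappa come from the experts' diagnoses. The net reclassification index is calculated after classification by a specialist who has interviewed and examined the patient, and so has the patient's age.
- **The study is exploratory and small.** Forced terms are not free with about 30 patients in the smaller group. This is a reason to force age only and leave sex optional.

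**Conclusion.** The point holds as an inexpensive improvement to the second objective, and by extension to the third. The stated tests are unadjusted, the stated models name no age term, and nothing in the design balances age.

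The consequence depends on an age gap that the documents do not quantify. Under the assumptions above, the false-positive rate for a marker with no disease signal is 6–53% for gaps of 0.25 to 0.75 SD, against about 5% after adjustment. Power for a true 0.8 SD marker falls to 19–78% when the gap runs the other way, against 84–99% after adjustment. For a small gap, such as 3 years on the log-scale assumptions, the effect is modest: 7–14% and an AUC of 0.53–0.56. With no gap there is none.

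The point does not reach the sensitivity, specificity, kappa or net reclassification results, and it does not make the crude comparisons invalid.

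**What to change.** 1. Keep the crude PD–AP comparisons, and report age by group beside them.
2. For continuous CSF and quantitative MRI markers, add the age-adjusted PD–AP difference from a linear model, on the log scale where the marker is skewed.
3. State that age enters as a forced first block in the MRI and CSF logistic models, before forward selection. Sex may be added but is optional, given about 30 patients in the smaller group. Scored MRI signs are then adjusted through this block.
4. Report each model's C-statistic alongside that of age alone, so that the gain from the scan or the lumbar puncture can be read directly.
5. If the same methods serve the third objective, apply the same rule there.

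This changes analysis wording only and uses demographics already collected. It costs one degree of freedom per model, and the gain in C-statistic over age may look less favourable than the crude figure. If the full analysis plan already forces age into these models, the article needs only a sentence saying so.

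### C-statistics of the three forward-stepwise models, taken from the 60 to 70 patients used to select the variables, will be optimistic and not comparable across strategies

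*Protocol article*

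**What the plan says.** The Statistical analysis section (protocol article, Methods/design) takes up the second objective after the accuracy analysis. It describes univariate comparisons of PD with AP and then states, for each of the three strategies, that "blockwise logistic regression with stepwise forward model selection will be used to identify parameters with optimal diagnostic power". It continues: "For each model ROC-curves and C-statistics are calculated". No entry or removal criterion is given.

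The Sample size calculation section says that "a minimum of 30 AP and 30 PD patients will be needed" and arrives at the statement that "approximately 100 participants will be needed". It draws on a previous cohort in which "60% of patients had a diagnosis of AP" and "30% of patients did not complete the follow-up period of 3 years". Of the 46 drop-outs there, 33 had AP.

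The candidate variables are listed in the sections on clinical examination, MRI and CSF. The article describes no second cohort or hold-out sample.

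**The concern.** Forward selection keeps the variables that happen to separate the groups best in the sample at hand. A C-statistic from that sample counts the lucky part of the separation as accuracy. The error is large when candidates are many and patients few, and it grows with the number of candidates.

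The three blocks have lists of different length, so their C-statistics would be inflated by different amounts. Two things are at stake. Variables reported as discriminating may be noise, which undermines an objective whose purpose is to find such variables. And one C-statistic per strategy invites a side-by-side reading, since the Background and Discussion present the study as a guide to the most useful investigation.

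**Working it through.** **1. Number of completers.** Inputs are from the Sample size calculation section: 60% AP, 30% drop-out, 33 of 46 drop-outs AP and hence 13 PD.

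- PD completers per patient enrolled: 0.40 − 0.30 × 13/46 = 0.315
- AP completers per patient enrolled: 0.60 − 0.30 × 33/46 = 0.385
- Enrolment needed for 30 of each: max(30/0.315, 30/0.385) = max(96, 78) = 96

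This agrees with the stated figure of approximately 100. At 100 enrolled, about 38 AP and 32 PD complete, 70 in all. The stated minimum is 30 + 30 = 60.

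**2. Candidates per block** (counted from the lists).

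- CSF: 11, or 8 where the three neurotransmitter metabolites are dropped because of dopaminergic medication.
- MRI: about 19 conventional signs, plus an unstated number of DTI, SWI and rs-fMRI measures.
- Clinical: about 27 (11 scales, about 10 questionnaire topics, about 6 examination items), and more if items or subscores are used.

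Patients in the smaller group (30 to 32) per candidate:

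- CSF: 30/11 to 32/11 = 2.7 to 2.9
- Conventional MRI: 30/19 to 32/19 = 1.6 to 1.7
- Clinical: 30/27 to 32/27 = 1.1 to 1.2

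**3. Size of the optimism.** Forward logistic selection was simulated with entry at p < 0.05 (score test), removal at p > 0.10, at most 12 variables, independent normal candidates and 200 runs per setting. The apparent C was compared with the C in 2000 new patients; optimism is the difference. The entry p is an assumption, borrowed from the significance level in the same section.

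With 38 AP and 32 PD:

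| Candidates | No signal: apparent C (true 0.50) | Three real markers, 0.7 SD each: apparent v new patients | Optimism | Optimism, markers 0.5 SD | Optimism, 0.7 SD, correlation 0.3 (150 runs) |
|---|---|---|---|---|---|
| 11 | 0.57 | 0.82 v 0.75 | 0.07 | 0.09 | 0.10 |
| 19 | 0.62 | 0.83 v 0.73 | 0.10 | 0.14 | 0.14 |
| 27 | 0.67 | 0.86 v 0.72 | 0.14 | 0.17 | 0.16 |
| 50 | 0.77 | 0.91 v 0.68 | 0.23 | 0.25 | 0.22 |

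At the 30 + 30 minimum with 0.7 SD markers, the optimism is 0.09, 0.12, 0.16 and 0.25. With 0.5 SD markers it reaches 0.19 at 27 candidates.

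A separate simulation with two real markers of 0.6 SD at 38/32 gave these apparent v new-patient values:

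- 11 candidates: 0.73 v 0.65 (optimism 0.08)
- 19 candidates: 0.76 v 0.65 (0.11)
- 27 candidates: 0.78 v 0.64 (0.14)
- 40 candidates: 0.82 v 0.62 (0.20)

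**4. Comparability.** Give two blocks the same three real markers (0.7 SD). The 27-candidate block then looks better than the 11-candidate block by 0.86 − 0.82 = 0.04, and does worse in new patients by 0.75 − 0.72 = 0.03.

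**5. Does correction work?** Bootstrap correction with the selection repeated was tried at 38/32 with three real markers of 0.7 SD (40 data sets, 40 resamples each):

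| Candidates | Apparent C | Corrected C | C in new patients |
|---|---|---|---|
| 11 | 0.82 | 0.74 | 0.76 |
| 27 | 0.85 | 0.72 | 0.72 |
| 50 | 0.91 | 0.75 | 0.69 |

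It removes most of the optimism at 11 and 27 candidates but under-corrects at 50, so the list must also be kept short.

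**The case against.** The strongest reply is that the main comparison lies elsewhere. For the first objective, diagnoses made by the specialist, the neuroradiologist and the neurochemist are set against the reference diagnosis by sensitivity, specificity and kappa, and MRI and CSF are then assessed by NRI. Variable selection enters none of these. A reader might infer that the planned comparison of the three strategies is biased. The article does not support that, because it nowhere says that model C-statistics will rank the strategies. This part of the objection stands.

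Two other strong readings also fail.

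- A reader might conclude that the longest list will look best whatever its true value. In simulation, 27 noise candidates gave an apparent C of 0.67 and 50 gave 0.77, both below the 0.82 of an 11-candidate block with three real markers of 0.7 SD. Reversal of the true order can happen but need not. Nor is it known which list is longest, since the number of advanced MRI measures is not given.
- A reader might assume that the univariate tests feed the stepwise selection. The article does not say so.

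It is also fair to say that a condensed article may leave internal validation to a fuller plan, so its absence here is not an error in itself. What remains is what the article does fix: forward selection from long lists in a small single cohort, and a C-statistic for each resulting model. The study's exploratory status lowers the stakes. It does not remove the problem, because finding discriminating variables is a declared objective.

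**Conclusion.** The point holds for the second-objective models only. Carried out as written, with C-statistics from the patients used for selection, the analysis overstates discrimination by about 0.07 to 0.17 for 11 to 27 candidates at 38/32 (somewhat more at 30/30), and by about 0.2 or more for 40 to 50. Noise variables may be selected, and the three C-statistics cannot be compared with each other.

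These sizes rest on an assumed entry p of 0.05, on simulated normal markers although the MRI signs are scored as present or absent, and on candidate counts tallied from the lists. That the C-statistics come from the same patients is inferred from the absence of any second data set. A fuller plan with optimism correction would answer much of the point. The first-objective results are not affected. Because the analysis is secondary and the study exploratory, the point ranks below a must-fix.

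**What to change.** In the Statistical analysis section:

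- Pre-list a short candidate set of similar size for each block, including the advanced MRI measures.
- Report C-statistics corrected for optimism by bootstrap, with at least 500 resamples and the whole selection repeated in each. Alternatively, use penalised logistic regression with the same internal validation.
- Set the blocks side by side only on corrected values and in the same patients. MRI and lumbar puncture have separate exclusions, and metabolite results are dropped for medicated patients, so the blocks could otherwise rest on different subsets.
- State that uncorrected C-statistics will not be used to rank the strategies.

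The cost is a script outside the standard SPSS menus and lower reported C-statistics. No new data are needed.
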